#### Abdominal phase

##### Step 1: Abdominal access

After a safe access to the abdominal cavity, confirmation of the absence of metastatic disease and judgement of the technical resectability is mandatory.

##### Step 2: Hepatoduodenal ligament and celiac axis 

Dissection of lymph node tissue along the common hepatic artery (LN 8a and optional 8p), the celiac artery (LN 9), the left gastric artery (LN 7) and the proximal splenic artery (LN 11p) is mandatory. The dissection of lymph node tissue along the proper hepatic artery (LN 12a) and the left side of the portal vein (LN 12p) is optional. The left gastric vein (close to the portal vein) and the left gastric artery (at its origin from the celiac artery) must be ligated and divided, followed by the dissection of the lymph node tissue from the left side of the celiac artery to the left crus at the oesophageal hiatus and left side of Gerota’s fascia.

##### Step 3: Gastric mobilization

Division of the greater omentum to enter the lesser sac, ensuring that the right gastroepiploic vessels are preserved to provide the blood supply to the gastric tube. Dissection along the greater curvature of the stomach towards the spleen, dividing the short gastric and left gastroepiploic vessels until the left diaphragmatic crus is reached. In doing so, the associated lymph node tissue (LN stations 4sa and 4sb) remains attached to the later specimen.

##### Step 4: Splenic artery

Ligation of the posterior gastric vessels if present at their origin. Afterwards, the optional dissection of the lymph node tissue along the anterior surface of the splenic artery (LN 11d) and the splenic hilum (LN 10) can be performed.

##### Step 5: Gastric tube formation

The lesser curvature of the stomach is cleared of LN tissue at the appropriate level, until the expected distal resection margin is reached (LN stations 3a and 3b). The gastric tube is created according to local standards (usually with linear staplers). This may also be performed in the chest depending on the local standard. The staple line of the gastric conduit can be oversewn if standard in the centre. A pyloroplasty, pyloromyotomy, or other may be performed if necessary.

##### Step 6: Diaphragmatic hiatus

Mobilization of the oesophagus from the diaphragmatic hiatus (LN 20) to the gastroesophageal junction (GEJ), resecting the right and left paracardial lymphatic (LN) tissue (LN 1 and 2). Transhiatal mobilization of the distal thoracic oesophagus with its surrounding (LN 110). Dissect along the pericardial adventitia to remove the pericardial tissue (LN 111). In advanced diseases, the right and left pleura can be resected. Dissect along the pre-aortic fascia (LN16a1 and 112aoA).

##### Step 7: Surgical adjuncts and closure 

Mandatory are the confirmation of haemostasis and the closure of the abdomen. Optional are the placement of a feeding jejunostomy, abdominal drain(s) and an abdominal lavage.

#### Thoracic phase

##### Step I: Thoracic access

The thoracic phase starts with a safe access to the patient’s right chest according to local standards.

##### Step II: Thoracic lymphadenectomy

Ligation and division of the azygos arch and divide the inferior pulmonary ligament. The dissection along the pericardium until the left lung is reached, including resection of the left pleura in advanced disease to achieve a clear circumferential margin is mandatory. Dissection is continued until the transhiatal dissection plane (abdominal part) is reached. Identify and ligate the thoracic duct above the level of the diaphragm, such that it is resected with the specimen. Perform a sub-carinal lymphadenectomy (LN 107). Clear both bronchi of LN tissue (LN 109). The dissection along the right pulmonary veins, continuing posteriorly until the left pulmonary veins are reached, is optional. Dissection of the mediastinal pleura at the anterolateral border of the thoracic aorta and the pre-aortic fascia, from the proximal resection margin towards the diaphragm (LN station 112). Dissection of lymph node tissue along the aorto-pulmonary window, clearing the arch of the aorta, pulmonary artery and recurrent laryngeal nerve as it hooks around the arch of the aorta (106tbL, 106recL, 105), is optional. Ligation of the thoracic duct at the proximal resection margin.

##### Step III: Specimen excision

Ensure that the thoracic part of the specimen is circumferentially free, from the previously completed diaphragmatic mobilization (performed during the abdominal phase) to above the level of the azygos vein (LN 108, 110 and 111). Deliver the stomach into the right chest cavity, ensuring that the gastric tube can reach the site of anastomosis without tension or torsion. Excise the specimen with suitable proximal and distal resection margins via the preferred way.

##### Step IV: Thoracic anastomosis

Perform an oesophagogastrostomy using your preferred method (stapler or suture).

##### Step V: Surgical adjuncts and closure

A nasogastric or nasojejunal tube may be placed. Thoracic drain(s) may be placed prior to the closure of the thoracic incision. After confirmation of haemostasis, the lung must be re-inflated under direct vision. Closure of the chest should be performed according to the local standard.

In the control group, the elective oesophagectomy will be performed as HYBRID-E, i.e. the abdominal phase of the operation will be performed minimally invasively while the thoracic part will be performed as open surgery (via a thoracotomy). The essential surgical steps performed in the control intervention are the same as for the experimental intervention and are outlined above.

### Criteria for discontinuing or modifying allocated interventions {11b}

Conversion to open surgery cannot be completely avoided, since reasons for conversion may arise intraoperatively, e.g. technical difficulties or bleeding. A low number of conversions reflect clinical reality and will not disappear even after the completion of the learning curve. Reasons for conversion will be captured for further evaluation of this subgroup. An overall conversion rate of <5% is expected for each study group. Patients undergoing conversion to open surgery (abdominal or thoracic part) remain in the trial and will be analysed in the modified intention-to-treat population.

If another type of surgery (other than abdominal and right thoracic oesophagectomy, Ivor-Lewis procedure) is indicated for complete tumour resection (e.g. transhiatal extended gastrectomy or abdomino-cervical oesophagectomy), the patient remains in the trial and will be followed up for the entire trial period. This is meaningful, because these types of surgeries constitute major operations, are associated with major complications and oncological outcome parameters can be analysed. The MICkey trial randomization will occur preoperatively, as intraoperative randomization is impractical due to the need for different operative set-ups (e.g. preparation of robot/laparoscopic towers) and patient preparation. To minimize bias, two intraoperative exclusion criteria have been defined. As a consequence, intraoperative exclusion of previously randomized patients might occur:*Case 1 (intraoperative diagnosis of previously occult metastases that prohibit surgical resection according to current S3 guidelines)* [19]: In this case, patients in both groups will undergo diagnostic laparoscopy only, as the abdominal part of the operation is the same in both groups and will be performed minimally invasive in both groups. Diagnostic laparoscopy is a minor surgery, with very few associated complications. Consequently, follow-up for the primary endpoint (comprehensive complication index) makes no sense, as it adds nothing to answering the primary research question, namely which surgical technique is associated with less complications after oesophagectomy, an operation which is associated with major complications. In addition, almost all secondary endpoints are meaningless in patients undergoing diagnostic laparoscopy only. Therefore, these patients will be excluded from the study. These patients will be defined as “intraoperative drop-out”. However, in line with the current S3 guidelines [19], patients with newly diagnosed intraoperative “sehr limitierter Fernmetastasen” (very limited metastases), which are “gut resektabel” (easily resectable), oesophagectomy in combination with resection of this “kleine, gut resektable Metastase” (small, well-resectable metastasis) should be performed [9] (recommendation 8.13). In this case, the patient remains in the trial and is regularly followed up.*Case 2 (tumour resection technically impossible)*. As for case 1, follow-up of patients makes little sense as these patients will undergo minor surgery only and DFS cannot be measured. Again, these patients will be defined as “intraoperative drop-outs”.The occurrence of both cases (case 1 and case 2) is assumed to be equally distributed between both study groups.

### Strategies to improve adherence to interventions {11c}

As MICkey is investigating two surgical interventions, strategies to improve adherence to the intervention are unnecessary as the patient cannot “withdraw” from the intervention during surgery.

### Relevant concomitant care permitted or prohibited during the trial {11d}

Additional treatments including all perioperative procedures are performed according to institutional standards and will be recorded to adjust for possible confounders in both groups.

### Provisions for post-trial care {30}

The post-trial care of the participants will be analogous to the regular tumour follow-up. Compensation is not provided.

### Outcomes {12}

#### Primary outcome/endpoint and assessment of primary outcome

The primary endpoint is overall postoperative morbidity within 30 days postoperatively measured via the comprehensive complication index (CCI) [17, 18]. The CCI ranges from 0 to a maximum of 100; the index expresses the cumulative morbidity that the patient experiences. The CCI is based on the established Dindo-Clavien classification (DCC) [22, 23]. A complication is any deviation from the normal postoperative course. The score is validated for oesophageal surgery, and a difference of 10 is regarded as a clinically relevant difference [18]. An endpoint reflecting the entire spectrum of complications like the CCI is highly appropriate to compare two different strategies like in the MICkey trial. The score will be calculated comprising all complications within 30 days.

A list of oesophagectomy-specific complications will be provided for all trial centres to facilitate documentation and assessment of postoperative morbidity according to the Esophagectomy Complications Consensus Group (ECCG) and the Dindo-Clavien grading system (Supplement 2) [24].

As postoperative oesophagogastroduodenoscopies (EGD) are frequent after oesophagectomy and performed routinely in some centres, a purely diagnostic EGD showing no pathological finding does *not* constitute a complication in the MICkey trial. Only if an endoscopic intervention (e.g. EndoVAC placement) is performed or a pathologic finding is identified on EGD (e.g. anastomotic leakage defined as “a full thickness GI defect involving oesophagus, anastomosis, staple line, or conduit irrespective of presentation or method of identification”) does this constitute a complication in the MICkey trial.

In the Addendum to the ICH E9 guideline, the estimand framework is recommended as a clear and transparent definition of “what is to be estimated” (International Council for Harmonization, 2019). An estimand is defined through the treatment, the targeted population, the variable (i.e. the endpoint), a specification of how to handle intercurrent events (post-randomization events) and a population-level summary. In the following, the primary estimand corresponding to the primary objective is described.

#### Treatment

Total minimally invasive oesophagectomy (MIN-E, either via “classical” minimally invasive laparoscopy and thoracoscopy or via robotic-assisted minimally invasive oesophagectomy [RAMIE] or any combination of the two) (experimental arm) vs. HYBRID-E (laparoscopic/robotic abdominal surgery and open thoracic surgery) (control arm)

#### Population

The targeted population is defined through the inclusion and exclusion criteria (incl. intraoperative exclusion criteria).

#### Variable

Overall postoperative morbidity in terms of the comprehensive complication index (CCI) within 30 days after surgery

#### Intercurrent events (ICE)

Specific events (e.g. death, re-operation) which can occur after randomization will be handled within the primary endpoint definition reflecting a composite strategy. Intraoperative deaths will be graded as grade V complication according to Dindo-Clavien. Treatment switcher from laparoscopic/robotic to open can occur and will be handled according to the intention-to-treat principle (treatment policy approach). Other intraoperative events can lead to an exclusion from the population (see intraoperative exclusion criteria).

Other post-randomization events will not be considered. This reflects a treatment policy approach, which means estimating the effect of randomized treatment irrespectively of other post-randomization events not captured in the primary endpoint definition.

#### Summary measure

The difference in mean CCI between study groups

#### Secondary outcomes/endpoints and assessment of secondary outcomes

90-day mortalityRate of re-operations within 90 days related to the index operation. Not included are planned elective surgeries not related to the index operation, e.g. port implantation.Pulmonary complications within 30 days postoperative according to Esophagectomy Complications Consensus Group (ECCG) definition [24]. See Supplement 2 for definitions and grading of pulmonary complications.Anastomotic leak (AL) defined according to ECCG as “full thickness GI defect involving oesophagus, anastomosis, staple line, or conduit irrespective of presentation or method of identification” within 30 days [24]. See Supplement 2 for grading of AL according to ECCG and DCC.Conduit necrosis/failure within 30 days postoperative according to ECCG definition [24]. See Supplement 2 for grading of conduit necrosis/failure.Delayed conduit emptying requiring intervention or delaying discharge or requiring maintenance of nasogastric drainage > 7 days (ECCG definition) within 30 days postoperative [24].Chyle leak according to ECCG definition within 30 days [24]. See Supplement 2 for grading of the conduit chyle leak.Recurrent nerve injury (vocal cord palsy) according to ECCG definition within 30 days [24]. See Supplement 2 for grading of recurrent nerve injury.

#### Surgical outcome measures

9.Operative time (in minutes; from the start of first skin incision until the closure of last skin incision). The time for repositioning of the patient between abdominal and thoracic part is included.10.Length of hospital stay (in days from the day of surgery until discharge)11.Conversion to open surgery. Conversion to open surgery during any of the minimally invasive parts of the operation (abdominal or thoracic). Reasons for conversion will be documented in the eCRF.

#### Patient-reported outcome measures (PROM)

12.Overall pain at rest and during movement (Numeric Rating Scale, NRS) at visits 3–5. The NRS ranges from 0 “no pain” to 10 “pain as bad as you can imagine” or “worst pain imaginable”.13.Assessment of postoperative thoracic pain syndrome measured as pain in the chest at rest and while coughing (NRS, 0–10) at visits 3–10. Chronic postoperative thoracic pain syndrome is a common and debilitating complication after thoracic surgery and was thus included as an endpoint in our trial. HYBRID-E and MIN-E might have different rates of thoracic pain syndrome due to differences in surgical access.14.Quality of recovery according to QoR-15 at visits 3–5 [25]15.Quality of life measured via QLQ-C30 and QLQ-OES18 at visits 7–10

#### Oncological outcome measures

16.Total lymph node count17.Rate of microscopic negative resection margin (R0)18.Disease-free survival (DFS) defined as the time from randomization until disease recurrence (local recurrence or metastases) or death from any cause within 2 years. DFS was chosen because it is clinically one of the most relevant oncologic outcome parameters according to regulatory agencies [26, 27].19.Overall survival (OS) defined as the time between randomization and death from any cause within 2 years. OS was chosen because it is clinically one of the most relevant oncologic outcome parameters according to regulatory agencies [26, 27].

#### Safety measures

20.Rate of serious adverse events defined as postoperative complication Clavien-Dindo grades III–V within 90 days after surgical intervention.

### Participant timeline {13}

**Table Tabb:** 

**Visit**	**V1**	**V2**	**V3**–**5**	**V6**	**V7**	**V8**	**V9/V10**
	Before surgery	Surgery (day 0)	POD 2 (+1) POD 4 (+1) POD 7 (+2)	Discharge	POD 30 (±5)	POD 90 (±5)	12 months postop. 24 months postop.
	**Outpatient/inpatient**	**Inpatient**			**Outpatient**	**Outpatient or telephone/mail**	
Eligibility criteria	X						
Informed consent	X						
Baseline demographics and clinical data	X						
Randomization	X						
Surgical data		X					
Histopathology (lymph node count, R0-rate)		X					
Assessment of primary endpoint (CCI)			X	X	X		
Assessment of reoperations			X	X	X	X	X
Safety (SAE)			X	X	X	X	
Assessment of secondary, oesophagectomy-specific outcomes according to ECCG			X	X	X		
Length of hospital stay				X			
Pain at rest and during movement (NRS)			X				
Thoracic pain syndrome measured as pain in the chest at rest and while coughing (NRS)			X	X	X	X	X
Quality of recovery (QoR-15)	X		X				
Health-related quality of life (EORTC QLQ-C30 + OES-18)	X				X	X	X
Disease-free survival					X	X	X
Overall survival (including 90-day mortality)		X	X	X	X	X	X

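### Chest pain is scored from visit 3 to visit 10 but not before surgery, so the thoracic pain endpoint measures total postoperative chest pain and cannot be adjusted for its own baseline

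*Protocol article*

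**What the plan says.** The outcome list of the protocol article (Patient-reported outcome measures) sets the endpoint and its timing: "Assessment of postoperative thoracic pain syndrome measured as pain in the chest at rest and while coughing (NRS, 0–10) at visits 3–10". It gives the reason for including it: "Chronic postoperative thoracic pain syndrome is a common and debilitating complication after thoracic surgery and was thus included as an endpoint in our trial". It adds that "HYBRID-E and MIN-E might have different rates of thoracic pain syndrome due to differences in surgical access".

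In the visit table under Participant timeline {13}, the row beginning "Thoracic pain syndrome measured as pain in the chest at rest and while coughing (NRS" has no mark at V1 (before surgery) or V2 (surgery). It is marked at V3–5, V6, V7, V8 and V9/V10.

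The same table does collect patient-reported measures before surgery. The rows beginning "Quality of recovery (QoR-15" and "Health-related quality of life (EORTC QLQ-C30 + OES-18" are both marked at V1. The row beginning "Pain at rest and during movement (NRS" is not, but that item is used only at V3–5. The row "Baseline demographics and clinical data" is marked at V1, and the article names no pain item within it.

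For secondary endpoints, Methods for additional analyses {20b} plans description, effect sizes with 95% confidence intervals, and regression models with treatment fixed and centre random. It names no baseline value of the outcome as a covariate, and it rules out imputation in these analyses.

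**The concern.** The endpoint is presented as a complication of chest surgery that may differ by surgical access. That is a statement about pain that the operation causes. All patients have a tumour of the oesophagus or the oesophagogastric junction. The eligibility criteria do not exclude existing chest pain, and they exclude an earlier right thoracotomy only if it took place within the last 3 years. Some patients may therefore have chest pain before surgery, although the documents do not say how many.

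Without a score at V1, a patient whose pain is unchanged by surgery looks the same as one whose pain began with it. The baseline table cannot show whether the arms started level on chest pain. The usual gain from adjusting a repeated score for its own starting value is also unavailable. A later analysis plan can choose the model, but it cannot recover a score that was never asked for.

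**Working it through.** **1. Is the V1 score really absent?**

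| Measure | Outcome list | Visit table |
|---|---|---|
| Chest pain, rest and coughing | visits 3–10 | V1 blank, V2 blank, then V3–5 to V9/V10 |
| QoR-15 | visits 3–5 | V1 and V3–5 |
| QLQ-C30 and OES18 | visits 7–10 | V1, V7, V8, V9/V10 |
| Pain at rest and during movement | visits 3–5 | V3–5 only |

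The outcome list leaves out V1 even for measures that the table marks there, so the table decides. For chest pain the two agree: there is no V1 score. Chest pain is the only patient-reported measure followed to 24 months without a preoperative value.

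**2. The plan's own sample size, for context.** The chest-pain endpoint has no calculation of its own. For the primary endpoint, a difference of 10 with SD 20 gives a standardised difference of 10/20 = 0.5. A two-sided t-test at 0.05 with 80% power needs 63.8, so 64 per group (power 80.1%). Allowing for 15% loss, 64/0.85 = 75.3, so 76 per group and 152 in total. The stated figures reproduce, and this point does not affect them. I use 64 per group below as the evaluable number.

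**3. Precision lost.** With correlation r between the V1 score and a later score, adjustment multiplies the variance of the treatment effect by 1 − r². Without adjustment, the standard error in SD units is √(2/64) = 0.177. The documents give no r; 0.2 to 0.5 is assumed.

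| r | 1 − r² | Less variance | Equivalent sample size, 1/(1 − r²) | Standard error |
|---|---|---|---|---|
| 0.2 | 0.96 | 4% | 1.04 | 0.173 |
| 0.3 | 0.91 | 9% | 1.10 | 0.169 |
| 0.5 | 0.75 | 25% | 1.33 | 0.153 |

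**4. Chance imbalance.** The difference in baseline means has the same standard error of 0.177 SD, so chance alone allows up to 1.96 × 0.177 = 0.35 SD with 95% probability. An imbalance of that size would shift the later difference by r × 0.35, which is 0.07 SD at r = 0.2 and 0.17 SD at r = 0.5. This is the same loss as in step 3 seen from another side, not an additional one.

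**5. What a V1 covariate does under a no-imputation rule.** If a proportion m of patients lacks the V1 score and is dropped, the variance factor becomes (1 − r²)/(1 − m). That exceeds 1, so the adjusted model is worse than no adjustment, once m is greater than r². The threshold is 4% missing at r = 0.2 and 25% at r = 0.5. A covariate added part-way through recruitment therefore needs its own rule for missing values.

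**The case against.** The protocol does not contradict itself here: text and table agree, and no stated analysis becomes impossible, because no baseline-adjusted analysis is promised for this endpoint. That stands. The point is an improvement to the design, not an error in it.

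The tumour is resected in everyone in the modified intention-to-treat set, so pain caused by it need not persist. That stands too. It argues for a low correlation, and so for the lower end of the range.

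Related information may be held in the V1 questionnaires or the baseline clinical data. The article names no chest-pain item there, and neither is shown to be the same score at rest and while coughing. At best this is a partial substitute.

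A reader might infer that existing pain biases the comparison or pulls the difference in rates towards zero. The documents do not support this. Existing pain is balanced in expectation by randomisation, so the difference in mean scores is unbiased for total postoperative chest pain. Attenuation of a rate would need a cut-off defining a case and existing pain that persists after surgery. The article gives no cut-off and no prevalence.

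A reader might also infer that this is the outcome on which chest access is expected to matter most. The outcome list says only that rates might differ, and the trial's main expectation concerns overall morbidity.

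**Conclusion.** The point holds as a minor one. No preoperative chest-pain score is collected, although the visit and the questionnaires to attach it to already exist. The randomised comparison remains valid for total chest pain after surgery. Three things are lost: telling new pain from existing pain, seeing a chance imbalance at baseline, and a reduction in variance of 4% to 25%. That range rests wholly on the assumed correlation of 0.2 to 0.5 and on a linear model for the score. The primary endpoint and the sample size are unaffected.

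**What to change.** Add the same two items (chest pain at rest and while coughing, 0–10) at V1, asked before randomisation, and include the V1 score as a covariate in the chest-pain models.

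For patients enrolled before the change, state a rule for this baseline covariate only: a missing indicator or mean imputation. Say explicitly that it is an exception to the no-imputation rule for secondary endpoints, so that nobody leaves the analysis. Because the missing value precedes treatment, such a rule leaves the randomised comparison intact.

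For patients without a V1 score, describe the endpoint as total postoperative chest pain, not as pain newly caused by surgery. If enrolment is already complete, this wording is the only part of the fix still available.

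The cost is two extra questions at an existing visit with one eCRF field each, and an amended schedule. The downside is that patients already enrolled will have no baseline value, so the gain in precision shrinks with their share.
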